### Study procedure

Women in the first trimester (before 12 + 6 weeks gestation) attending antenatal care clinics providing ultrasonographic examinations will be approached by members of the study team and asked to participate. Women will be fully informed about the study objectives and procedures. Only women who sign a consent form will be enrolled into the study.

Fetuses will be scanned in the first trimester for the estimation of gestational age and subsequently at monthly intervals for fetal biometry [17].

All infants will receive an anthropometrical assessment after delivery, including measurement of birth weight [18]. All pregnant women in the study will be administered a 24-hour dietary recall at entry into the study, and at approximately 28 and 36 weeks gestation, to assess maternal nutritional status and ensure that women enrolled in the study have an adequate diet and that nutrient intake is in accordance with current pregnancy recommendations [18,19]. At each visit, the obstetric history of participating women will be updated to collect information related to pathological processes that may affect fetal growth, and blood pressure and proteinuria will be measured.

No additional procedures will be added to routine antenatal care provided at the study centres, with the exception of 4–5 additional ultrasonographic examinations and three repeat 24-dietary recalls.

### Dating by ultrasound

Gestational age will be confirmed by measuring the crown-rump length (CRL) between 8 + 0 to 12 + 6 weeks based on LMP. Gestational age (GA) by CRL should agree with GA by LMP to within 7 days. If LMP and CRL agree, CRL measurement will be used for dating. The average of three measurements will be used. If GA by CRL and GA by LMP differ by more than 7 days, the woman is not eligible for the study.

To acquire the CRL measurements, the midline sagittal section of the whole fetus will be visualized with the fetus horizontal on the screen at 90 degrees to the angle of insonation [20]. GA will be assessed by using the reference charts published by Robinson and Fleming [19].

### Fetal biometry

The first visit (dating scan) will be between 8 + 0 and 12 + 6 weeks, and subsequent visits for fetal biometry will be scheduled at approximately 4 weekly (+/− 1 week) intervals at 14, 18, 24, 28, 32, 36, and 40 weeks. All scanning appointments will be arranged at the time of the dating scan and study enrolment. All participants will be scanned in the lateral recumbent position.

The compulsory ultrasound measurements to be obtained at all visits include the following biometrical parameters:

•Biparietal diameter (BPD)

•Head circumference (HC)

•Abdominal circumference (AC)

•Femur length (FL)

•Transcerebellar diameter (TCD)

•Humerus length (HL)

•Fetal Foot length (FFL)

At each examination, all measurements are to be obtained three times from three separately generated ultrasound images and uploaded electronically (with the associated images) to the data management system. The mean of the three measurements of each parameter will be used for clinical management purposes as per local protocols.

In addition, a full morphological evaluation (abnormality scan) will be conducted at 18–24 weeks following standard practices at each centre. Fetuses diagnosed with any minor abnormalities will be managed according to local clinical guidelines. If the clinical decision is to continue with the pregnancy the case will remain in the study. Fetuses with major abnormalities that may affect morphometric measurements will be excluded from further study. All infants will receive an anthropometrical assessment after delivery [21].

The following measurement techniques will be used:

•Biparietal Diameter-Technique: Measured from the outer-outer (BPD 1) and outer – inner (BPD 2) edges of the parietal bones in a cross-sectional view of the fetal head at the level of the thalami and cavum septum pellucidum or cerebral peduncles. The cerebellum is not to be included. The measurement should be obtained from an image with the midline echo as close as possible to the horizontal plane with the angle of insonation of the ultrasound beam at 90 degrees.

•Head Circumference -Technique: Obtained from the same image as BPD as follows: Measurement of occipito-frontal diameter (OFD) obtained by placing calipers on the outer borders of the occipital and frontal edges of the skull at the point of the midline across the longest part of the skull. The ellipse facility will be used to calculate HC as above.

•Abdominal Circumference - Technique: The sonographer will visualize the transverse section of the fetal abdomen as “close as possible” to circular including the stomach and the junction of the umbilical vein and portal sinus. The anterior-posterior (A-P) and transverse diameters will be measured with calipers placed on the outer borders of the body outline. The A-P diameter will be measured from the spine to the anterior abdominal wall and transverse diameter at a right angle to the A-P diameter. The ellipse facility will be used to calculate AC as outlined above.

•FL-Technique: Measured from an image of the full femoral shaft in a plane as close as possible to a right angle to the ultrasound beam. The distal femoral epiphysis is to be excluded.

•Transcerebellar Diameter (TCD): the TCD can be imaged from the sub-occipito-bregmatic view of the fetal skull, and measured from the second trimester onwards. The calipers will be placed on the outer-outer margins of the cerebellar poles.

•Humerus length (HL): Measured from an image of the full humeral shaft in a plane as close as possible to a right angle of insonation.

•Fetal Foot Length (FFL): Fetal foot length will be measured from the second trimester onwards. The foot is measured from either sagittal or plantar views. The measurement is taken from the skin overlying the heel (calcaneus) to the end of the longest toe.

### Ultrasound volume acquisition protocol

The ultrasonographic equipment that will be used in the study will allow for acquiring and storing 3-dimensional images. This feature is of critical importance for data quality purposes. Stored 3-dimensional images (volumes) could be used at a later stage to retake measurements that have been identified as erroneous.

Except for a transvaginal scan during the first research visit (8 0/7 -12 6/7 weeks), 3D volume data will otherwise be acquired using a transabdominal probe. All volumes shall be systematically labelled using the comment feature of the Voluson E8 (GE Healthcare, Germany) Expert system (e.g. “LA1”).

Recommended Image settings:

•At least High Quality 2

•CRI no greater than 2

•No speckle reduction (SRI)

•Harmonic imaging as needed

•Acoustic focus adjusted for the anatomic region

•Use the widest image window to capture the volume of interest, depending on fetal activity

•Adjust the magnification and image depth settings to fill at least one-half of the screen

### Training

As done in previous studies [3,22] sonographers participating in the study will receive specific training and will be certified as proficient under the supervision of a qualified instructor, according to a standard protocol. Intra-observer and inter-observer measurement errors will be assessed according to a published protocol before the initiation of the study during the training period [21]. We will consider estimating a learning course [23].

All instruments and techniques to be used in all centres will be standardised, i.e. equipment and training will be provided to each of the measurement teams. Equipment specifications to be considered are the following: i) Commercially available high quality real-time ultrasound scanner; ii) Less than 2 years old; iii) T/V and abdominal probes suitable for scanning throughout pregnancy; iv) Facility for on-line transfer of measurements and associated images; v) Facility to “blind” measurements from examiner until after data transfer.

Site visits to the study centres will be organized in order to provide lectures and update courses by experts in the field. In addition during site visits, standardization sessions will be carried out according to repeat-measure protocols to assess the accuracy and precision of the anthropometrical measurements in mothers and newborns.

### Neonatal anthropometrical assessment

Neonatal body composition assessment during the first 24 hours will be used to determine the growth outcome of each pregnancy on the basis of multiple postnatal measurements in order to be able to relate pre- and postnatal anthropometrical measurements. After delivery, a trained investigator will take standardized measurements of the head circumference, abdominal circumference (superior border of umbilicus), and thigh circumference (at the skin crease located midway between the knee and trunk with the lower leg at about 90 degrees in relation to the thigh measured in centimetres) with non-stretchable tape. The crown-heel length will be obtained by placing the supine infant, with extended legs, on a plastic newborn length board (Statiometer, Ellard Instrumentation, Seattle, WA, USA). Skin fold caliper measurements (Harpenden) will be used to document soft tissue distribution [17,24]. These skin folds will include the triceps fold, anterior thigh fold, sub-scapular skin fold, and abdominal flank skin fold that will be made at each site twice and averaged. This data will be used to estimate per cent body fat and lean body mass as an index of neonatal growth outcome. Other parameters of neonatal body composition will include ponderal index and birth weight [25].

### Nutritional assessment

Adequate nutrition is one of the major requirements for selecting populations eligible for the study. Therefore, the assessment and maintenance of adequate nutritional status is considered a critical component of the study activities.

At three times during the study follow-up (at entry and at approximately 28 and 36 weeks) the nurse/nutritionist, trained in collecting anthropometric and diet data, will assess maternal nutritional status *via* anthropometry (weight, height, arm circumference, head circumference, skinfolds) (Table 1), as well as assessing the dietary intake (by twenty-four-hour recall). Measurements will be carried out by a female nurse/nutritionist in a private room according to the procedures described by Gibson [17]. The time of the examination will be recorded to allow for diurnal variations. Having only one person performing the measurements will minimize inter-examiner errors. The equipment required is already available at the study site.

**Table 1 T1:** Description of maternal anthropometric measures

**Measure**	**Procedure**
Weight	Weight will be measured using a beam balance with nondetachable weights. Weight will be recorded to the nearest 0.1 kg [26].
Height	Height will be measured in the standing position using a stadiometer and recorded to the nearest millimetre. If the reading falls between two values, the lowest millimetre will be recorded [26].
Mid-upper arm circumference	Measurements will be taken using a flexible fiberglass tape wrapped around the upper left arm, at the midpoint between the acromion process and the tip of the olecranon. Measurements will be recorded to the nearest millimetre [26].
Head circumference	A flexible fiberglass tape will be used. The tape will be placed above the supra-orbital ridges and over the part of the occiput which gives the maximum circumference. Measurements will be taken to the nearest millimetre [26].
Skinfolds	Left triceps and left scapular skinfolds will be taken using a Lange skinfold thickness caliper. The combination of one body and one limb skinfold to assess body fat is recommended by most investigators [26].

Dietary intakes will be assessed using 24-hour recalls; specifically a trained nutritionist or nurse will query the study participants on foods and beverages consumed by them in the previous 24-hours. Information will also be collected on portion sizes as well as preparation methods. This information will then be linked with appropriate country-specific food composition tables to arrive at estimates of macro and micro-nutrients [27,28]. This method results in the attainment of estimates of the intake of single nutrients. Compliance is high because the respondent burden is low. The interview takes approximately twenty minutes. The quality of the information collected is dependent on the respondent’s motivation and ability to recall intakes and on the interviewing skills of the nutritionist/nurse. Repeated twenty-four-hour recalls on the same individual allow estimations of the individual’s usual dietary intake over a long period of time [28]. In our study the twenty-four-hour recall will be repeated three times for each woman. This method has been successfully used in previous studies focusing on nutrition, fetal growth and other pregnancy outcomes conducted by investigators who are taking part in the proposed study.

### Safety of ultrasonographic assessment

Ultrasonography in pregnancy is considered a safe procedure and in more than 30 years no fetal harm has been reported with use in the low-intensity range of gray-scale imaging (no Doppler), which is the technology that will be used in the proposed study [29]. Serial ultrasonography for research purposes according to schedules similar to the one we propose has been approved previously in the context of other studies [30-33].

Following a recommendation of the WHO Scientific and Ethical Review Group, we conducted a systematic review and meta-analysis to evaluate the safety of human intrauterine exposure to ultrasonography [32].

We systematically searched electronic databases, reference lists and unpublished literature according to the following criteria:

•Types of studies: Trials and observational studies that assessed short and long term effects of exposure to ultrasonography during pregnancy.

•Types of participants: Women submitted to ultrasonography in pregnancy and their offspring.

•Types of exposure: B-mode or Doppler sonography during any period of pregnancy, for any number of times, using any equipment and transducers.

•Types of outcome measures: 1) adverse maternal outcomes, 2) adverse perinatal outcomes, 3) abnormal childhood neurological development, and 4) childhood malignancies.

The electronic search identified 6716 citations and 63 were selected for full text evaluation. Additionally, 19 citations were identified from secondary sources. A total of 58 references reporting data of 38 different studies were included: 16 clinical trials, 11 cohorts, and 11 case controls. Ultrasonography in pregnancy was not associated with adverse maternal effects, impaired physical or neurological development or increased risk for malignancies in childhood. According to the clinical trials, there was a weak association between exposure to ultrasonography and non-right handedness in boys (OR 1.26, 95% CI 1.03-1.54) and a slight decrease in mean neonatal length (WMD −0.26 cm, CI −0.45, −0.07) and head circumference (WMD −0.15 cm, CI-0.29, −0.01). In conclusion, based on the available evidence, exposure to diagnostic ultrasonography during pregnancy appears to be safe.

### Sample size

The total sample size will be 1400 pregnant women and their infants. Each country centre will collect data from 140 women. This number is sufficient for the development of local centile growth charts with a high level of precision, accounting for exclusions to final analysis due to inability to follow up and occurrence of pregnancy complications [34,35].

The sample size needed for the estimation of a specific percentile was computed using the following formula [36]:

$$n=\frac{\left(1+z_{\alpha }^{2}/2\right)}{{\left(\frac{\%\mathrm{SE}\;P_{\alpha }}{\%\mathrm{CV}}\right)}^{2}}$$

where z_α_ is the standard normal deviation corresponding to the percentile being estimated, % SE C_α_ is the expected percentage standard error of the percentile and % CV is the percentage coefficient of variation. Sample sizes were computed for 5 different parameters (biparietal diameter, abdominal and head circumference and femur and humerus length) and for 3 different percentiles: 5%, 10% and 50%. Information about the coefficient of variation was obtained from data on serial ultrasonographic examination conducted on approximately 500 pregnancies in the context of the WHO randomized trial of calcium supplementation in low intake women [37]. Additionally, the expected half-width of the confidence interval with a sample size n = 100 was computed.

Table 2 shows the levels of precision obtainable with a sample size of 100 women for various biometrical parameters. In addition the proposed sample size of 140 women per centre will allow for testing for differences in growth patterns across centres [38].

**Table 2 T2:** Levels of precision obtained with a sample size of 100 women for some biometrical fetal parameters (values and half widths in mm)

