**Abdominal circumference**										
Week	Mean	10% Centile	5% Centile	CV	%SE_50	%SE_10	%SE_5	Width_50	Width_10	Width_5
20	147.7	133.5	128.8	7.9	0.79	1.07	1.21	2.33	2.85	3.12
24	190.7	173.8	166.6	7.4	0.74	1.00	1.14	2.82	3.47	3.78
28	235.2	215.4	210.6	6.4	0.64	0.86	0.98	3.01	3.72	4.13
32	278.6	255.8	248.3	6.5	0.65	0.88	1.00	3.62	4.49	4.95
36	314.5	288.0	277.9	7.1	0.71	0.96	1.09	4.47	5.52	6.05

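### Table 2 converts the 5th- and 10th-centile standard errors to millimetres with the centile instead of the mean, so those half-widths are printed 3% to 16% too small

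*Protocol article*

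**What the plan says.** The Sample size section of the protocol article sets 140 women per centre and presents this as enough for precise local charts after exclusions. It introduces its method thus: "The sample size needed for the estimation of a specific percentile was computed using the following formula". The formula is n = (1 + z²/2) / (%SE / %CV)². The numerator term of the ratio "is the expected percentage standard error of the percentile and % CV is the percentage coefficient of variation". It was applied "for 3 different percentiles: 5%, 10% and 50" per cent, for five biometric parameters. The section then adds: "Additionally, the expected half-width of the confidence interval with a sample size n = 100 was computed".

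Table 2, titled "Levels of precision obtained with a sample size of 100 women for some biometrical fetal parameters (values and half widths in mm", gives, for each parameter at weeks 20, 24, 28, 32 and 36, the mean, the 10th and 5th centiles, the CV, three percentage standard errors and three half-widths in mm. The first row, for abdominal circumference (AC), reads "20 147.7 133.5 128.8 7.9 0.79 1.07 1.21 2.33 2.85 3.12". Neither the base of the percentage nor the confidence multiplier is stated.

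The Data analysis section plans polynomial regression for the mean and a separate model of the SD from absolute residuals. It does not mention working on a log scale.

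**The concern.** A CV is an SD divided by a mean. If %SE is obtained by scaling a CV, it is a standard error expressed as a percentage of the mean, and it returns to millimetres by multiplying by the mean. Multiplying by a lower centile gives a smaller number. The printed lower-centile widths look as if they were made that way.

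Table 2 is the numerical support shown for the precision of local charts. The affected entries are the lower centiles, which are the ones used to identify small fetuses, and every one errs in the favourable direction. Local charts matter because the Discussion foresees local or ethnically specific standards if centres differ.

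**Working it through.** **Inputs.** From the Sample size section: n = 100 and the formula above. From Table 2: mean, centiles, CV and printed half-widths. From the normal distribution: z = 1.645 (5th) and 1.2816 (10th) in absolute value, so √(1 + z²/2) = 1.534 and 1.350; for the 50th it is 1.

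**Step 1: reproduce the percentage standard errors.** Rearranged, %SE = CV × √((1 + z²/2)/100). For AC at week 20: 7.9 × 0.1350 = 1.07 (10th) and 7.9 × 0.1534 = 1.21 (5th), as printed. All 75 entries reproduce, with a largest difference of 0.005, which is rounding.

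**Step 2: reproduce the printed half-widths.** Carrying unrounded %SE for AC at week 20:
- 50th: 2 × 0.79% × 147.7 = 2.33, as printed.
- 10th: 2 × 1.066% × 133.5 = 2.85, as printed.
- 5th: 2 × 1.212% × 128.8 = 3.12, as printed.

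Over the table, 2 × %SE × centile matches all 50 lower-centile entries within 0.9%. For the 50th centile the table uses the mean, and all 25 entries match within 1%.

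**Step 3: check the base of the CV.** For AC at week 20, (147.7 − 128.8)/1.645 = 11.5 mm, which is 7.8% of the mean 147.7, against a printed CV of 7.9. The CV is on the mean.

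**Step 4: recompute on the mean.** Half-width = 2 × %SE × mean.

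| Parameter, week | Centile | Printed (mm) | On the mean (mm) | Ratio |
|---|---|---|---|---|
| AC, 20 | 10th | 2.85 | 3.15 | 1.105 |
| AC, 20 | 5th | 3.12 | 3.58 | 1.147 |
| AC, 36 | 10th | 5.52 | 6.03 | 1.092 |
| AC, 36 | 5th | 6.05 | 6.85 | 1.132 |
| Head circumference, 36 | 5th | 3.77 | 4.09 | 1.085 |
| Humerus length, 20 | 10th | 0.67 | 0.75 | 1.126 |
| Humerus length, 20 | 5th | 0.74 | 0.86 | 1.159 |
| Femur length, 36 | 10th | 0.58 | 0.60 | 1.032 |
| Femur length, 36 | 5th | 0.64 | 0.68 | 1.063 |

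Ratios use unrounded widths on the mean. Over all rows they run from 1.032 to 1.126 at the 10th centile and from 1.055 to 1.159 at the 5th. The recomputed value is larger in all 50 entries.

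**Step 5: sensitivity to the multiplier.** With 1.96 instead of 2, the widths on the mean still exceed all 50 printed values, by 1.1% to 10.3% (10th) and 3.4% to 13.5% (5th).

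**Step 6: simulation.** For a normal variable with mean 147.7, CV 7.9% and n = 100, the simulated standard error of the estimated 5th centile was 1.793 mm, against 1.790 mm from SD × √((1 + z²/2)/n). Doubled, this is about 3.58 mm, not 3.12.

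**Step 7: number of women for the printed widths.** Since width varies as 1/√n, n = 100 × ratio². The smallest is 100 × 1.032² = 106.5, so 107. The largest is 100 × 1.1585² = 134.2, so 135.

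**The case against.** The best defence is a log-scale reading. The text speaks of the percentage standard error of the percentile, which taken literally is a percentage of that percentile. If the measurements are roughly log-normal, the CV approximates the SD of the logarithm, the standard error of the log centile is CV × √((1 + z²/2)/n), and the centile is the right base. For AC at week 20 this gives 2.84 and 3.12 mm, practically the printed values. The tabulated centiles do not exclude it. Centiles predicted from the printed mean and CV are closer under the log-normal model in 34 of 50 cases, and the mean absolute error is about equal (0.62 mm log-normal, 0.61 mm normal). This part stands as a possibility. It is not the analysis described, however, because Data analysis models the mean and SD with no log transformation mentioned.

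Without a log scale, the literal wording does not rescue the table. A percentage of the centile would need SD/centile in the formula in place of the CV. The %SE columns would then be too small by the same factor, and the corrected millimetre widths would be those in the table above.

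The remaining objections concern importance, and they largely stand. The largest change is 0.80 mm. No target half-width is set, so none is missed. Table 2 treats each week alone, whereas the planned regression uses all visits, so the fitted centiles will not have exactly these widths.

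A reader might infer that 140 women per centre are too few, or that local charts will be imprecise. The document does not support either inference. Even the worst entry needs 135 women for its printed width, which is below 140. How wide an interval n = 100 gives on the percentile scale depends on n and z alone and has nothing to do with this error.

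**Conclusion.** The point holds as a minor numerical correction. Under the stated formula and the mean-and-SD modelling described, the half-widths for the two lower centiles are understated in all 50 entries, and the 50th-centile column is right. The correct width is 1.03 to 1.13 times the printed one at the 10th centile and 1.06 to 1.16 times at the 5th.

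This rests on three assumptions: measurements approximately normal on the millimetre scale, CV equal to SD/mean (which Table 2 bears out), and a multiplier of 2, inferred from the table. The direction does not depend on choosing 2 or 1.96. It does depend on the scale: if a log-scale model was intended, the printed widths are about right and the defect is that the document does not say so.

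**What to change.** Recompute the 10th- and 5th-centile half-width columns of Table 2 as multiplier × %SE × mean, and replace the printed values. Name the multiplier used and state that %SE is a percentage of the mean. Alternatively, if a log-scale model is intended, say so in both Sample size and Data analysis, so that the centile is a valid base and the columns can stay.

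The cost is two table columns, or a sentence in each of two sections. No more women are needed, and the design and analysis are unchanged. With the first option the stated precision becomes slightly less favourable.
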